#### Subgroup analysis

Sociodemographic characteristics: body mass index, age (≥ 40 years; and < 40 years), sex, recommendations for surgery, driving, headache, depression, number of sick leave days from work;Physical examination: neurologic examination (sensory loss, muscle weakness), pain upon range of motion (ROM) (i.e. flexion, extension, lateral bending, rotation);Pain characteristics: area of neck pain (bilateral/unilateral, central/trapezius/back), existence of radiating pain (yes/no, unilateral/bilateral, pain under the elbow joint, pain in the back), pain characteristics (acute onset versus slow onset, persistent versus aggravating), conditions of pain aggravation (understress, fatigue), nocturnal pain;Treatment prior to study: experience of Chuna manual therapy, continuation of physical therapy or conventional medication;Expectancy and preference for treatment: credibility and expectancy, preference (Chuna manual therapy; usual care; or no preference);X-ray examination: head forward posture, lateral deviation of spine, cervical intervertebral disc space, degenerative change;Index severity evaluation: VAS ≥ 7 and < 7, NDI high/low.

All statistical analyses were performed with SAS version 9.4 statistical package (SAS Institute, Cary, NC, USA), with the level of significance set at *p* < 0.05.

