### Outcomes

#### Primary outcome measurement

The primary outcome will be the visual analogue scale (VAS) of the past three days’ neck pain. VAS refers to an evaluation tool that records the degree of pain the patient feels with one end indicating no pain and the other end indicating the most severe pain imaginable on a 100 mm line [18, 19]. Participants will be asked to mark the one point that best describes his or her neck pain during the previous week.

The difference in VAS at baseline (visit 2) and the primary endpoint (follow-up 1 [visit 11]: five weeks after visit 2) will be used to compare the two groups to identify the difference in effect size.

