### Sample size

Calculation of number of participants required for the clinical trial: for calculation of significant number of participants, the following is hypothesized based on the previous literature:Level of significance, α = 0.05;Type II error (β) is set at 0.2 with power of the test set at 80%;According to a previous clinical study using VAS as the main assessment tool for Chuna manual therapy in neck pain patients, the effect size of Chuna manual therapy in comparison to the control can be considered to be 1.03 [30], and 1.49 [31], respectively;Compliance rate will be set at 85% (the predicted rate of receiving ≥ 6 sessions of treatment during the five-week treatment period);For calculation of sample size, G*Power 3.1.7 was used. With evidence from item (3), application of mean ± SD resulted in conservatively hypothesizing the effect size of this clinical trial as 0.6 because of the high clinical heterogeneity of manual therapies such as Chuna. Application of items (1) and (2) and the effect size resulted in the calculation of a sample size of 90 participants (45 in each group).The mean comparison of pain requires a total of 90 participants (45 in each group), which is the minimum number of participants needed for testing the abovementioned hypothesis. Considering that 15% of participants received < 6 sessions of treatment within the five-week treatment period, a total of 108 participants, 54 in each group, will be extracted for the study.

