Specific timepoints where the VAS and NRS fall under the half line point of the baseline standard will be performed for a comparative analysis on patient improvement rate. To measure the time between random allocation to the point when neck pain improves to less than half the original pain intensity, Kaplan–Meier survival analysis will be used for analysis and the curve will be compared using the log-rank test. A Cox model will be used to calculate the hazard ratio to compare the speed at which pain improves to less than half the original pain. Whether the recovery speed differs by subgroup will also be examined.

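### About 35 unranked subgroup factors fall under a blanket 0.05 level in a 108-patient trial, and the severity cut at VAS 7 does not fit the 100 mm scale

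*Protocol article*

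**What the plan says.** The Subgroup analysis section of the protocol article names factors under seven headings: sociodemographic, physical examination, pain characteristics, prior treatment, expectancy and preference, X-ray, and index severity. One run of the sociodemographic entry reads "recommendations for surgery, driving, headache, depression, number of sick leave days from work". No factor is ranked above another and none is called exploratory. The paragraph directly under the list covers all statistical analyses, "with the level of significance set at *p* < 0.05".

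The Statistical analysis section takes subgroups into the time-to-improvement analysis as well: "Whether the recovery speed differs by subgroup will also be examined".

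The last subgroup heading begins "Index severity evaluation: VAS" and splits patients at 7, with no unit. Under Primary outcome measurement the VAS is a 100 mm line, "with one end indicating no pain and the other end indicating the most severe pain imaginable". The 0 to 10 scale in the protocol belongs to a different instrument, the NRS. Entry requires an NRS of at least 5; there is no VAS entry threshold.

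**The concern.** There are two separate problems in one short section.

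The first is error control. A long, unordered list tested at an unadjusted 0.05 in a trial sized only for its main comparison is likely to produce some nominally significant subgroup by chance, and is poorly placed to find a real one. The Discussion says the trial should inform clinical practice guidelines and insurance coverage. It ties those uses to the trial as a whole, but a subgroup result labelled significant could travel with the main result.

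The second is an internal contradiction. A cut at 7 makes sense on a 0 to 10 scale but not on a 100 mm line. An analyst who applied it literally would put practically every patient in the upper stratum, and the only pain-intensity split on the list would then be uninformative.

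**Working it through.** **Inputs.** From Sample size: "Level of significance, α = 0.05"; "Type II error (β) is set at 0.2 with power of the test set at 80"%; "conservatively hypothesizing the effect size of this clinical trial as 0.6"; 45 evaluable and 54 randomised per arm; 85% compliance. From Subgroup analysis: the factor list and the 0.05 level.

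**The plan's own figure.** A two-sample t-test with two-sided alpha 0.05 and d = 0.6 needs 45 per arm (power 0.804), which matches the stated 90. Sidedness is not stated; one-sided gives 35 per arm (normal approximation), so two-sided is the reading that reproduces the plan. Inflation: 45/0.85 = 52.9, so 53 per arm and 106 in total, against 108 stated. The main sample size is sound.

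**Counting factors.**

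| Heading | Factors |
|---|---|
| Sociodemographic | 8 |
| Physical examination (2 neurological, 4 movements) | 6 |
| Pain (area 2, radiation 4, onset and course 2, aggravation 2, nocturnal 1) | 11 |
| Prior treatment | 2 |
| Expectancy and preference | 2 |
| X-ray | 4 |
| Severity | 2 |
| Total | 35 |

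The total is 34 to 37 depending on how compound items are split.

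**False positives, one test per factor, one outcome, no true subgroup effects.**

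- Expected number: 35 × 0.05 = 1.75. This does not depend on correlation between the tests.
- Chance of at least one, independent tests: 1 − 0.95^35 = 0.834. For 34 to 37 factors it is 0.825 to 0.850.
- Simulation with a common correlation between the 35 test statistics (the correlations are assumptions; the protocol gives none):

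| Assumed correlation | Chance of at least one |
|---|---|
| 0.1 | 0.82 |
| 0.3 | 0.71 |
| 0.5 | 0.54 |

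**Power for a treatment-by-subgroup interaction.** Take all 108 patients, 54 per arm, a two-level factor with prevalence p, outcome SD of 1 and a normal approximation. Then SE = sqrt(2/(54p) + 2/(54(1 − p))) and power = Φ(0.6/SE − 1.96).

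- p = 0.5: SE = sqrt(4/27) = 0.385; 0.6/0.385 − 1.96 = −0.40; power about 34%. The interaction detectable with 80% power is 2.80 × 0.385, about 1.08 SD.
- p = 0.2: SE = 0.481; 0.6/0.481 − 1.96 = −0.71; power about 24%.

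The effect of 0.6 is borrowed from the planned main effect as a yardstick; the protocol states no interaction size.

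**The VAS cut.** Read as 7 mm, the boundary lies at 7% of the line. Patients who rate their pain 5 or more out of 10 at entry would very rarely mark below it. Read as 7 on a 0 to 10 metric, it equals 70 mm, and both strata can fill. The document does not say which is meant.

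**The case against.** Several points on the other side are fair.

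- **Dependence.** The factors are visibly related: pain on four neck movements, and several descriptors of radiating pain, some of which apply only to patients who have it. A reader might infer from a list this long that a false subgroup claim is nearly certain. The documents do not support that. The 83% needs independence, and the figure falls as correlation rises. About 97% (1 − 0.95^70) is reached only by assuming two independent tests per factor, which the protocol does not specify.
- **Method of testing.** A reader might infer that treatment effects will be tested within each stratum, because no interaction test is mentioned. No subgroup test of any kind is stated, and the one sentence that poses a question asks whether recovery speed differs by subgroup, which fits an interaction term. Nor does the section say that every outcome will be analysed by subgroup; only recovery speed is linked explicitly.
- **Condensed article.** The choice of test and an exploratory label may properly sit in an analysis plan that is not shown, so their absence is no finding. What stands is what the article does say: a long unranked list followed directly by one significance level for all analyses.
- **Power.** The trial claims no subgroup power, and low power is ordinary at this size. The 34% shows no error in the sample size; it shows why a significance rule is unsuitable for this list.
- **The VAS stratum.** A reader might conclude that the lower stratum is empty. That depends on reading 7 as millimetres, and even then entry is by NRS, so the stratum would be near-empty rather than certainly empty. A slip from a 0 to 10 metric is the likelier explanation. The mismatch with the 100 mm definition remains on either reading.

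**Conclusion.** The point holds in a limited form. About 35 unranked factors under an unadjusted 0.05 level give 1.75 expected false positives for one outcome when no subgroup effects exist. The chance of at least one is high: 83% under independence, and still above one half at an assumed common correlation of 0.5. Against that, power for an interaction as large as the planned main effect is about 34% with an even split and complete data on 108 patients, and less with uneven splits.

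The severity cut is a separate inconsistency with the protocol's own scale. It leaves the split undefined in unit and, if taken in millimetres, practically one-sided.

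The primary comparison and its sample size are unaffected. Both matters are worth correcting before analysis.

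**What to change.** State the severity cut in the unit of the 100 mm VAS: 70 mm if 7 on a 0 to 10 metric was intended, which the sponsor must confirm.

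Add a sentence that takes the subgroup list out of the general 0.05 rule. For each factor, report the treatment-by-subgroup interaction estimate with its confidence interval, from the ANCOVA for continuous outcomes or the Cox model for time to improvement, and label these results exploratory.

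This changes wording only and needs no extra patients or data. The price is that no subgroup result can be called significant. Naming a few priority factors in advance would be reasonable but is a matter of preference, and the correction does not depend on it.

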### Economic evaluation

Economic evaluation will be performed simultaneously with the clinical study to determine the cost-effectiveness of Chuna manual therapy and usual care. The primary economic outcome will be cost per quality-adjusted life years (QALY) gained. The primary economic endpoint will be  set for the study period and for the follow-up period; when estimation for time after this period is needed, it will be by extrapolation of cost and effect using a regression model or secondary analysis that performs decision modeling analysis. Treatment fees from the clinical trial will be calculated by combining the number of treatment sessions and unit fees, where the unit fee will be based on data from national health insurance and fees as charged at the study sites. Estimation of quality of life for calculation of QALYs will use quality of life estimates as deduced by EQ-5D-5 L as the evaluation variant; the AUC method will be used. When the time horizon exceeds 12 months, the fee unit will be standardized to 2017 Korean currency (Won) applying a 5% discount based on the economic evaluation guideline of HIRA. The analytic viewpoint of this study is from a social standpoint; representative values (mean) of the parameters used in the study will be used in baseline analysis. Sensitivity analysis will be performed through probabilistic sensitivity analysis using all possible estimated parameters and representative values.

### Data collection and management

Paper CRFs and electronic CRFs (e-CRFs) utilizing an Internet-based Clinical Research and Trial management system (iCReaT) provided by the Korea Centers for Disease Control & Prevention will be used. Standard operating procedures (SOPs) will be prepared before initiation of the clinical trial. Investigators at supervising organizations will train the outcome assessors and investigators at each study site on how to fill out CRFs, convert electronic data, and adhere to the SOP. CRF data relating to outcome indexes will be entered by double data entry and data entry will be performed at each clinical trial site and supervising sites. After double confirmation of data transfer, all investigators, with the exception of the statistician, will be blocked from data access.

### Adverse events

Adverse events refer to undesirable and unintentional signs (i.e. abnormal laboratory test results), symptoms, or disease occurring after treatment during the process of the clinical trial, which does not have to have a causal relationship with the treatment intervention. Investigators will analyze the frequency of AEs, abnormal laboratory test results, and severe adverse events (SAEs). All description of SAEs will be recorded. AE information will be collected through symptom reports from patients and observations of investigators; occurrence frequency between groups will be analyzed.

Any phenomenon considered to be due to AEs associated with treatment (e.g. symptoms, onset, duration) will be recorded without exception in the investigation forms; what is not recorded will be considered a subjective symptoms. In addition, since the evaluation of AEs may expose the participant allocation group, the evaluation of AEs will be recorded in a separate CRF by the study coordinator; evaluation of the severity of AEs will be based on the evaluation standard for AE severity. Assessment of the causal relationship with treatment will follow the WHO-UMC causality scale and will be categorized into six steps for evaluation (1, definitely related; 2, probably related; 3, possibly related; 4, probably not related; 5, definitely not related; and 6, unknown). After consultation with the study investigators on abnormal laboratory findings, the degree of subjective/objective symptoms will be divided into three levels as proposed by Spilker et al.: Mild (1), no need for additional procedures and no great interference with the subject’s everyday life (function); Moderate (2), significant interference of the subject’s everyday life (function), probable need for additional procedures but followed by resolution after the procedure; and Severe (3), SAEs calling for advanced procedure, and leaving sequelae) will be applied for evaluation.

The researchers responsible for clinical trial conduction at each study site are obligated to explain the possibility of potential AEs that may occur after treatment intervention to the study collaborators, participants, and/or guardians. Educational training sessions on how to report any symptoms of potential AEs occurring after treatment will be provided. Any local, general, or pathophysiologic symptoms should be recorded and classified by symptom type, onset, severity, additional procedures, progress, and causal relationship with the treatment intervention according to the management standard of the clinical trial and also recorded in the participant CRF. The principal investigators at each study site should describe and evaluate any symptoms that occurred during the study period, and any SAE occurring over the study period should be reported to the Institutional Review Board (IRB) of that study site and the supervising clinical trial site (Jaseng Medical Foundation) for determination of continuation or termination of the study. Additional safety information should be reported periodically until the relevant AE is resolved (i.e. resolution of the relevant AE or unavailability for follow-up). The principal investigators at each study site will adhere to the Declaration of Helsinki when performing the clinical trial.

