### Data monitoring and safety monitoring

The safety of participants will be reviewed; the CRFs and evidence documents will be compared for certification of completeness of data.

Monitoring will be scheduled for three timepoints: upon recruitment of study participants; in progress during the study period; and upon completion of the clinical trial. Monitoring sessions will be performed by the personnel responsible for monitoring at the supervising study site.

All AEs reported during the study period will be noted to calculate the incidence of AEs. The proportion of participants with AEs in each group will be calculated and compared using Chi-square test or Fisher’s exact test.

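### The adverse-event recording sentence conflicts with the protocol's own cause-free AE definition and all-symptom recording rule, and should be reworded to match them

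*Protocol article*

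**What the plan says.** The Adverse events section of the protocol article contains several statements on what counts and what is recorded.

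- **Definition.** An AE is an undesirable, unintended sign, symptom or disease arising after treatment, "which does not have to have a causal relationship with the treatment intervention".
- **Source.** "AE information will be collected through symptom reports from patients and observations of investigators; occurrence frequency between groups will be analyzed".
- **Recording sentence.** "Any phenomenon considered to be due to AEs associated with treatment (e.g. symptoms, onset, duration) will be recorded without exception in the investigation forms". With its closing clause, the duty is that such phenomena "will be recorded without exception in the investigation forms; what is not recorded will be considered a subjective symptoms".
- **Causality.** A six-step scale is applied, which includes "4, probably not related; 5, definitely not related; and 6, unknown".
- **Severity.** The degree of subjective as well as objective symptoms is graded in three levels.
- **Later paragraph.** "Any local, general, or pathophysiologic symptoms should be recorded and classified by symptom type, onset, severity", with causal relationship among the attributes to be classified. Site principal investigators are also to describe and evaluate any symptom that occurs during the study.

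The section Data monitoring and safety monitoring then sets the analysis: "All AEs reported during the study period will be noted to calculate the incidence of AEs". The proportion of participants with AEs is compared between groups by the chi-square or Fisher's exact test.

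**The concern.** Two entry rules are stated for the same data. Under the definition and the later paragraph, a symptom is recorded first and its relation to treatment is graded second. The recording sentence puts its unconditional duty on a narrower class, which can be identified only after someone has judged association with treatment. Its second clause then expects some phenomena to go unrecorded and gives them a label, subjective symptoms, that elsewhere in the section belongs inside AE evaluation.

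The order matters because the trial is open-label. The Blinding section says that practitioner and participant cannot be blinded. The study coordinator records the AE evaluation on a separate form. Coordinators also assign the randomized numbers when envelopes are opened, so they probably know the allocation, although this is an inference from role titles. A judgement of association made before entry would therefore be made with knowledge of the arm. An event omitted at that stage may not be recoverable, and later causality grading cannot restore it.

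Safety is a named objective, and the Background faults earlier manipulation studies for lacking a systematic AE reporting system. With five sites, different sites could also read the two rules differently.

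**Working it through.** The point is textual. The documents state no AE rate, AE margin or power for the AE comparison, so there is no figure to reproduce.

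**1. Definition against recording sentence.** The definition includes events with no causal link to treatment. The recording sentence promises unconditional recording only for phenomena considered associated with treatment. An event judged unrelated is an AE by the first statement and is not covered by the duty in the second. The sentence does not forbid recording it; it leaves it outside the guarantee.

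**2. Recording sentence against later paragraph.** The later paragraph covers any local, general or pathophysiologic symptom and lists causal relationship as one attribute of what has been recorded. The sequence is record, then classify. The recording sentence implies classify, then record. Neither refers to the other.

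**3. Closing clause against the rest of the section.** Symptoms are part of the AE definition, patients' reports are a source, and subjective symptoms receive a severity grade. A label of subjective symptom therefore cannot mark an event as outside AE recording without contradicting all three.

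**4. Causality scale.** The scale has grades for probably and definitely unrelated events. These grades have a use only if unrelated events reach the form. This supports the broad rule and shows that the narrow sentence is out of line with it.

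**5. Analysis.** The comparison in Data monitoring and safety monitoring counts all reported AEs and is not restricted to related ones. That is the right numerator, but it can count only what was entered.

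**6. Can a size be derived?** Let p be the true proportion of participants with an AE, taken as equal in both arms, and let r1 and r2 be the fractions recorded in each arm. As a simplification, treat each affected participant as having one recordable event. The observed proportions are p × r1 and p × r2, and their difference is p × (r1 − r2). The documents give neither p nor either r. With 54 per arm (Sample size section), let q1 = p × r1, q2 = p × r2 and q = (q1 + q2)/2. The probability that a two-sided 5% test rejects is approximately

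Φ[(|q1 − q2| − 1.96 × SE0) / SE1], with SE0 = √(2q(1 − q)/54) and SE1 = √((q1(1 − q1) + q2(1 − q2))/54).

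Example, with assumed p = 50%, r1 = 100% and r2 = 80%: q1 = 0.50, q2 = 0.40 and q = 0.45, so SE0 = 0.0957 and SE1 = 0.0953. Then (0.10 − 0.1877)/0.0953 = −0.92, and Φ(−0.92) = 0.18.

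| Assumed p | Assumed recording fractions | Observed | Rejection probability |
|---|---|---|---|
| 30% or 50% | equal | equal | nominal 5% |
| 30% | 100% v 80% | 30% v 24% | about 10% |
| 30% | 100% v 60% | 30% v 18% | about 31% |
| 50% | 100% v 80% | 50% v 40% | about 18% |
| 50% | 100% v 60% | 50% v 30% | about 56% |

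The answer runs from no effect to a large one and is driven wholly by the assumed fractions. It shows that unequal recording would matter if it happened. It does not estimate this trial's error rate, and the direction of any imbalance is equally open.

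**The case against.** The strongest reply is that the protocol already requires broad recording and that one sentence, perhaps awkwardly translated, is being read too hard. The sentence never says *only*. Its bracketed examples (symptoms, onset, duration) are largely attributes of an event, so it may be meant as a rule on complete description. The definition, the sources, the unrelated grades on the causality scale and the later paragraph all point to recording regardless of cause. The separate AE form is there to protect assessor blinding. Operating procedures and site training on AE reporting, which are not shown, may settle the matter in practice.

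Most of this stands, and it rules out the stronger readings that a reader might infer:

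- **That the protocol captures only treatment-related events.** The text sets a minimum duty for one class and excludes nothing, and the later paragraph covers the rest.
- **That subjective symptoms are discarded.** The protocol does not say so, and it grades them.
- **That the between-arm comparison depends on unblinded attribution.** The analysis counts all reported AEs, and causality is one of the attributes classified for each recorded symptom. Unblinded ascertainment of AEs would remain after any rewording, since it comes from the open-label design and not from this sentence.
- **That a particular inflation of false positives or loss of power follows.** Every such figure needs recording fractions that the documents do not supply.

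The reply does not remove the inconsistency. That other text points the other way is what makes this sentence a contradiction. The closing clause has no reading that fits the rest of the section. A translation problem would explain the wording, but site staff would still have to choose between the two rules.

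**Conclusion.** The concern holds as an internal contradiction of moderate severity. The recording sentence and its closing clause disagree with the cause-free definition in the same section and with the later all-symptom rule.

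The consequence is conditional. If a site followed the narrower sentence, attribution would precede entry, and the AE proportions could be incomplete or differ between arms for reasons other than incidence. The documents do not show that this is the operative rule. No size or direction of bias can be derived from them, and the table under the working is illustration on assumed inputs only.

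The conclusion rests on the wording as published and on two assumptions: that no unseen operating procedure has already resolved the conflict, and that the coordinator who records AEs knows the allocation. The textual contradiction does not need the second assumption.

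**What to change.** Reword the recording sentence in Adverse events so that it agrees with the later paragraph of that section. For example: *Every untoward sign or symptom, subjective or objective, that is reported or observed after treatment starts is recorded in both arms regardless of presumed cause; its relation to treatment is graded afterwards on the six-step scale.* Delete the clause on what is not recorded.

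Carry the same wording into the operating procedures and site training, so that all five sites apply one rule. The comparison in Data monitoring and safety monitoring already uses all reported AEs and needs no change.

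The cost is an edit to the protocol and procedures and somewhat more AE entries per participant. It needs no new visits or staff.

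### The adverse-event severity grades build outcome and SAE status into intensity, so an event that is severe but recovers cannot be graded severe as the text stands

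*Protocol article*

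**What the plan says.** All the wording at issue is in the Adverse events section of the protocol article, with one related sentence under Data monitoring and safety monitoring.

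- **Mild (1):** "no need for additional procedures and no great interference with the subject’s everyday life (function". Nothing is said about how the event ends.
- **Moderate (2):** significant interference with everyday function, with "probable need for additional procedures but followed by resolution after the procedure".
- **Severe (3):** "SAEs calling for advanced procedure, and leaving sequelae".
- **Meaning of SAE:** among the quantities to be analysed by frequency the section lists "abnormal laboratory test results, and severe adverse events (SAEs". It expands the S as severe, and the article prints no separate seriousness criteria.
- **Handling of SAEs:** "All description of SAEs will be recorded", and "any SAE occurring over the study period should be reported to the Institutional Review Board (IRB) of that study site" as well as to the supervising site. Neither sentence sets a condition on sequelae or on grade.
- **Planned comparison** (Data monitoring and safety monitoring): "The proportion of participants with AEs in each group will be calculated and compared using Chi-square test or Fisher’s exact test".

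The Adverse events section also asks for each symptom to be classified by severity, by additional procedures and by progress as separate items.

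**The concern.** A severity grade should say how intense an event was. Whether it was serious, and how it ended, are different facts. Here grade 3 demands all of them together, and grade 2 has recovery written into it. Two consequences follow from the wording. An intense event that needed an advanced procedure and then recovered cannot be called severe. And grades 2 and 3 cannot be assigned until the outcome is known, although intensity is known when the event occurs.

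Safety is one of the trial's stated objectives, and the Background justifies the study partly by the lack of systematic adverse-event reporting in earlier manipulation and mobilization studies. At stake is whether a table of adverse events by grade can be taken at face value. A secondary question is whether the SAE count and the reports to the IRB are complete, since the SAE label and the top grade are worded in terms of each other.

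**Working it through.** The plan gives no figure to reproduce on this point. The check is one of wording, followed by tracing which analyses use the grade.

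**Step 1. The three definitions side by side**

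| Grade | Interference with function | Procedure | SAE required | Outcome required |
|---|---|---|---|---|
| Mild (1) | Not great | None | No | None stated |
| Moderate (2) | Significant | Probably needed | No | Resolution |
| Severe (3) | Not stated | Advanced | Yes | Sequelae |

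**Step 2. Types of event run through the definitions**

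| Event | Result as written |
|---|---|
| Slight, resolves | Grade 1 |
| Significant interference, procedure, resolves | Grade 2 |
| Intense, advanced procedure, recovers fully | Fails grade 3 for want of sequelae; grade 2 is the nearest fit |
| SAE, advanced procedure, sequelae | Grade 3 |
| Significant interference, does not resolve, not an SAE | Fails 1 (interference), 2 (no resolution) and 3 (not an SAE): no grade |
| Significant interference, outcome unknown | Cannot be placed in grade 2 or 3 |

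The last row can occur: the section itself foresees reporting that ends because the participant is no longer available for follow-up.

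**Step 3. Which planned analyses use the grade**

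- Proportion of participants with any AE, by arm: does not use it.
- Occurrence frequency of AEs between groups: no use of severity is stated.
- Frequency of SAEs: listed separately from the grade, but SAE is expanded as severe, the only printed description of severe is grade 3, and grade 3 is worded in terms of SAEs. The wording is circular.
- Any table by grade: uses it directly.

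**Step 4. Size, on assumed event counts**

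The article gives no event rates, so the counts below are assumptions, with at most one severe event per participant. Arm size is 54.

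- One event moved out of grade 3: 1/54 = 1.9 percentage points.
- Two to four truly severe events in an arm: 2/54 = 3.7% to 4/54 = 7.4%.
- Half of them recover: 1/54 = 1.9% to 2/54 = 3.7% remain in grade 3.
- All recover: 0%.

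Now take 6 severe events in one arm and 1 in the other, with the same share r recovering in each. Expected grade 3 counts are 6 × (1 − r) and 1 × (1 − r):

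| r | Grade 3, arm A | Grade 3, arm B |
|---|---|---|
| 0 | 6 | 1 |
| 0.5 | 3 | 0.5 |
| 0.8 | 1.2 | 0.2 |
| 1 | 0 | 0 |

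The absolute counts fall. The ratio stays at 6 to 1 for as long as any events remain.

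**Step 5. The any-AE comparison**

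With an assumed 20/54 against 12/54 participants having any AE, Fisher's exact test gives p = 0.14. Moving events between grades 3 and 2 leaves both counts, and so the p value, unchanged.

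**The case against.** The strongest reply is that the planned safety analyses barely depend on the grade. The one between-group test specified counts participants with any AE. SAEs are counted and described in their own right, and the reporting sentence covers any SAE without mentioning sequelae. The same paragraph asks for further reports until the event is resolved, so reportable events are expected to recover. Course and procedures are already recorded apart from severity. The scale is condensed from a cited source, and a journal article may leave the formal SAE definition and the CRF fields to the full protocol.

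Most of this stands, and it rules out several stronger readings that a reader might infer:

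- *That the safety comparison understates harm.* Not supported: the any-AE comparison does not use the grade, and the same rule applies to both arms.
- *That every event that resolves is capped at grade 2.* Too broad: a mild event that resolves fits grade 1, and grade 2 also needs significant interference.
- *That an SAE must leave sequelae, so recovered ones escape the IRB.* The article does not say so. The circular wording makes it a risk in practice and no more.
- *That the lack of a formal SAE definition is itself a fault.* It may sit in the full protocol, and no finding is made on that.

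What the reply does not remove is the printed rule. The grade definitions are stated in the article, and followed literally they misplace recovered severe events and leave some events ungraded. The ungraded case does not depend on reading SAE as serious in the regulatory sense: a persistent event of moderate intensity already falls between the grades.

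**Conclusion.** The point holds as a fault in the stated definitions. The scale combines intensity, seriousness and outcome. An event that is severe but recovers cannot be graded severe, and a significantly interfering event that neither resolves nor is an SAE has no grade. Any tabulation by grade would therefore understate severe events, by 1.9 percentage points of an arm for each participant whose only severe event is moved. How many would be moved is unknown, because the article gives no event or recovery rates. The conclusion rests on sites following the wording literally, and on a table by grade being produced, which the article does not state.

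The any-AE comparison is unaffected, and a biased contrast between arms is not shown. Under-counting of SAEs and of IRB reports is a risk created by the circular terms and is not a rule that the article states. The correction is worth making because safety is a stated objective and the change is small.

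**What to change.** 1. Define the three severity grades by intensity and interference with function only. Remove resolution, sequelae and SAE status from the grade definitions.
2. Record outcome, including resolution and sequelae, under the progress item that the Adverse events section already collects.
3. Record SAE status as a separate yes/no field that depends on neither grade nor sequelae, and reconcile the expansion of SAE with that field.
4. Key the report to the IRB and the supervising site to the SAE field.
5. Tabulate severity grade and SAEs separately by arm.

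The cost is a wording change, one added field on the separate adverse-event form already in use, and re-grading of any events already recorded, which can be done from their descriptions.
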